### Randomization after allocation procedure

We will employ stratified randomization, which is directed by a biostatistician. Participants with a MA score <.85 will be randomly assigned to either the treatment or control group by a computer-generated block randomization scheme. We will also stratify by moderate (84-70 %) and low (<70 %) adherence to maintain balance between the treatment and attention-control groups. Participant number is sequentially assigned in the order in which individuals are consented. If a Pp drops out in the intervention phase, the next enrolled Pp is assigned to the same group (treatment or attention-control) as the drop out was assigned. Although requiring RAs from both study groups to be available at study enrollments appears inefficient, in our experience it is a great advantage to engage new enrollees immediately in our treatment protocol and thereby eliminate potential attrition between randomization and the first intervention or control session.

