### Statistical analysis

Sample size and power calculations are based on comparing expected change in medication adherence rate of patients in each group at six months - an expected adherence mean difference of 10 % based on our pilot study findings and the literature. We use an alpha of .05 and provide for 90 % power to detect indicated effect sizes in this two-arm randomized study. An effect size difference of 70 % is based on a conservative estimate of our pilot work. A sample size of 46 older KT recipients per group (final total sample 92) will meet these assumptions and provide sufficient power. Recruitment and retention rates are calculated from our pilot study, other adherence studies at the same sites, and are documented in one similar RCT adherence study in older KT recipients [63, 64]. We selected an adherence rate of 85 % to divide the adherers from the non-adherers based upon our preliminary work describing 4 clusters of KT medication adherers: those who (1) take medications on time (1.0-.85 MA rate), (2) take medications on time with late/missed doses (.84-.70 MA rate), (3) rarely take medications on time and who were late with morning and/or evening doses (.69-.20 MA rate), and (4) missed many doses (<.20). Even minor deviations in dosing adherence lead to poor outcomes, though no studies have determined the criterion adherence “dose” that distinguishes good and poor outcomes.

Appropriate descriptive analyses will be performed to examine distributional characteristics for collected measures, as well as to summarize changes over time as a function of group assignment. During this initial phase, we will explore bivariate relationships among primary and secondary outcome measures and variables thought to affect medication adherence. In addition, we will conduct analyses to determine whether the randomly assigned groups are equivalent at the start of the study on the demographic and other measures collected at baseline. Before hypothesis-testing analyses are conducted, exploratory analyses will be performed to examine the effect of various mediators and moderators on the relationship between intervention, adherence, and clinical outcome. The results of these analyses will determine what additional variables will be incorporated in the subsequent hypothesis testing (e.g., analysis of covariance).

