Our primary analysis assesses whether the SystemCHANGE™ intervention is more effective than the attention-control intervention in increasing MA in adult kidney transplant recipients at the completion of the 6-month intervention and 6-month maintenance phases. We hypothesize that adult kidney transplant recipients receiving the SystemCHANGE™ intervention will have higher immunosuppressive MA rates than the attention-control group at the completion of intervention and maintenance phases. Since rate responses will most likely violate the normality assumption, the non-parametric method, Mann- Whitney test, will be used for comparing the two groups. However if the normal assumption is satisfied through transformation or as raw data measures, t-test will be applied for group comparison. Possible covariates resulting from demographic data and screening phase MA will be included in the analysis to adjust for possible bias.

Our secondary analysis assesses the MA patterns in both the SystemCHANGE™ and attention-control groups. Specifically we are interested in determining when the intervention becomes effective (e.g., what “dose” is needed) and the pattern of decay in MA over time in both groups. The dependent variable for these research questions are the repeated measurements of immunosuppressive MA rates at 12 time points [i.e. 1, 2, 3, 4, 5, 6, 7, 8, 9, 10, 11 and 12 months] and the independent variable is group assignment and time effect. Poisson regression analysis will be used for these questions. Proc Nlmixed procedure in SAS will be used for Poisson regression modeling. In order to answer the hypothesis we will test for group-by-time interaction to test if the two groups have different time profiles for MA or not. Possible covariates resulting from demographic data and screening phase MA will be included in the model to adjust for possible bias. Repeated measures from the same Pp will be accounted for using a random effect in the model.

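### The primary comparison names two tests that cannot carry the covariates it requires, and lets exploratory outcome analyses choose further covariates; one adjusted model should be fixed for months 6 and 12

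*Protocol article*

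**What the plan says.** All statements are in the protocol article.

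- **Default test** (Statistical analysis, primary analysis paragraph). Because adherence (MA) rates are expected to be non-normal, "the non-parametric method, Mann- Whitney test, will be used for comparing the two groups".
- **Switch** (same paragraph). "However if the normal assumption is satisfied through transformation or as raw data measures, t-test will be applied for group comparison". No criterion and no transformation is named.
- **Adjustment** (same paragraph). "Possible covariates resulting from demographic data and screening phase MA will be included in the analysis to adjust for possible bias".
- **Further covariates** (Statistical analysis, descriptive paragraph). Exploratory mediator and moderator analyses come before hypothesis testing, and their results decide which additional variables enter it. Analysis of covariance is given there as an example.
- **Time points** (Aims; Statistical analysis). The primary comparison covers the end of the intervention phase (month 6) and the end of the maintenance phase (month 12).
- **Randomisation** (Randomization after allocation procedure). "We will also stratify by moderate (84-70 %) and low (<70 %) adherence to maintain balance between the treatment and attention-control groups". Centre is not stated as a stratification factor.
- **Sizing** (Statistical analysis). "Sample size and power calculations are based on comparing expected change in medication adherence rate of patients in each group at six months", with a 10-point mean difference, an effect size of 70 % and 46 per group.

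**The concern.** A Mann-Whitney test and a two-sample t-test each compare two groups and have no place for a covariate. The primary paragraph names these two tests, then requires adjustment, and names no model that could do it. An analyst who follows the text must either drop the adjustment or replace the test. Either choice departs from part of the plan.

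Three features of the confirmatory result are also left to be settled after outcome data are seen: rank test or t-test, raw or transformed scale, and which covariates enter. The third matters most. The exploratory analyses that choose the covariates use the adherence outcome, and the candidates are mediators. Adjusting for a variable that the intervention may itself have changed can remove part of the treatment effect that the trial is meant to estimate.

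The named tests also do not deliver the quantity on which the trial was sized. Mann-Whitney gives no mean difference, and a t-test on a transformed scale gives none in percentage points.

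**Working it through.** **1. The statements side by side**

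| Place in Statistical analysis | Method named | Covariates | Chosen when |
|---|---|---|---|
| Primary paragraph | Mann-Whitney, or t-test | screening MA and possible demographic variables | test chosen after a normality check |
| Descriptive paragraph | analysis of covariance, as an example | whatever the exploratory analyses indicate | after outcome analyses |

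The first row cannot be executed with its own covariates. The second can, but its covariates are selected from the data.

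**2. Could a post-randomisation variable enter?** The mediators named in the text are social support and systems-thinking. Table 2 marks both in the intervention and maintenance columns, not under screening. The Design section places randomisation at entry to the intervention phase. Table 2 gives phases and not visits, so a measurement just before randomisation is not excluded. Nothing in the text restricts covariates to such values.

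**3. Is the stated sample size wrong?** Inputs from Statistical analysis: alpha 0.05, power 90 %, and the effect size, for which the section says "An effect size difference of 70 % is based on a conservative estimate of our pilot work", read here as d = 0.70. Sidedness is not stated; two-sided is assumed.

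- Two-sided t-test, exact: 43.87 per arm.
- Divided by the Mann-Whitney relative efficiency under normality, 3/π = 0.955: 43.87 / 0.955 = 45.94, rounded up to **46**, the stated figure.
- Power at 46 per arm: 0.913 (t-test), 0.900 (Mann-Whitney).

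The number reproduces as an unadjusted Mann-Whitney size.

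**4. What adjustment would do to power.** The correlation ρ between screening and follow-up MA is not given, so the values below are assumed.

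*Near-normal data, d = 0.70 on the follow-up scale.* Effective d = 0.70 / √(1 − ρ²), 46 per arm:

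| ρ | effective d | ANCOVA power |
|---|---|---|
| 0 | 0.700 | 0.913 |
| 0.3 | 0.734 | 0.936 |
| 0.5 | 0.808 | 0.970 |
| 0.7 | 0.980 | 0.996 |

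The comparator is 0.900 for Mann-Whitney.

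*If d = 0.70 is on the change scale*, as the sizing sentence suggests, effective d = 0.70 × √(2 / (1 + ρ)). ANCOVA power is then 0.985, 0.970 and 0.950 at ρ = 0.3, 0.5 and 0.7, against 0.913 for a t-test on change. Here the gain shrinks as ρ rises.

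*Left-skewed bounded data, simulated.* Assumptions: beta distributions, means 0.72 and 0.82, SD 0.143 (close to the implied 10 / 0.70 = 14.3 points), 46 per arm, 2,500 runs per setting. Plain ANCOVA used screening MA, stratum and centre; rank-based ANCOVA used screening MA.

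| ρ | Mann-Whitney | plain ANCOVA | rank-based ANCOVA |
|---|---|---|---|
| 0 | 94.3 % | 90.6 % | 94.1 % |
| 0.3 | 94.4 % | 90.8 % | 95.7 % |
| 0.5 | 94.8 % | 95.9 % | 98.5 % |
| 0.7 | 94.4 % | 99.2 % | 99.8 % |

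A repeat of this kind gave plain ANCOVA 93.0 % against 95.1 % for Mann-Whitney at ρ = 0.3. The loss at low ρ is therefore about 2 to 4 points.

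**5. What the normality switch does to type I error.** Choosing between t-test and Mann-Whitney by a Shapiro test gave 5.0 to 5.6 % in the same simulations. This covers the test switch alone. It does not cover a search over transformations or the outcome-driven choice of covariates.

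**The case against.** The strongest reply is that the plan does intend to adjust. A reader might infer that it throws away three months of screening adherence, but "Possible covariates resulting from demographic data and screening phase MA will be included in the analysis to adjust for possible bias" says the opposite. What is missing is a model, not the intention. It follows that the power difference between ANCOVA and an unadjusted Mann-Whitney test is not the cost of this defect. That stands.

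The section also mentions analysis of covariance, and an article may leave the normality criterion, the transformation and the covariate list to the full plan. This stands too, and none of those omissions is the point here. A later document can add detail, but the two statements would still have to be reconciled, because they lead to different primary analyses and one cannot be run.

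Three other stronger readings are not supported:

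- *ANCOVA is simply more powerful.* No correlation is given, and restricting the sample to MA below 85 % may lower it. The section itself expects non-normal rates, the kind of data in which plain ANCOVA can lose at low correlation.
- *The normality switch seriously inflates type I error.* The simulated switch moved it little.
- *The analysis omits centre as a randomisation factor.* Centre is not stated to be one. The stratum is a dichotomy of screening MA and adds little beside the continuous value.

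**Conclusion.** The point holds as a contradiction in the printed text. The primary analysis cannot be carried out as stated, and its test, scale and covariates are not fixed before outcome data are seen. The most consequential part is the route by which mediators measured after randomisation could enter the confirmatory test. Whether that would happen is not stated, but nothing prevents it.

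This conclusion does not rest on power. The 46 per arm stands, given two-sided alpha and d = 0.70. The gain from adjustment is conditional: about 0.94 to 0.996 against 0.90 under near-normal data, d on the follow-up scale and assumed ρ of 0.3 to 0.7. For skewed data and low ρ, plain ANCOVA may lose a few points, while rank-based ANCOVA was about equal to Mann-Whitney or better in every setting simulated. The skewed results depend on assumed distributions.

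**What to change.** Reconcile the two statements by fixing, before any comparison by arm, one primary model for both month 6 and month 12:

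- **Model.** ANCOVA of MA rate on arm and continuous screening-phase MA, plus the randomisation stratum, with robust standard errors. Centre is optional, but the choice should be made now. Report the adjusted difference in percentage points with a 95% CI.
- **P-value.** The section expects non-normal rates. If that means skew, state now that the p-value comes from rank-based ANCOVA on the same covariates. Do not leave this to a normality check.
- **Sensitivity analysis.** Keep the Mann-Whitney test, or a van Elteren test stratified by adherence level.
- **Remove.** The normality-based switch and the selection of covariates from exploratory outcome analyses. Allow only variables measured before randomisation. Mediator and moderator analyses stay with the exploratory aims.

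The cost is analysis-plan wording; screening MA is already collected on every participant and the sample size does not change. There are two downsides. Plain ANCOVA, if used for the test, may lose a little power under skew with low correlation. A rank-based p-value and an interval from plain ANCOVA may also disagree in a borderline case, so the plan should say that the p-value decides.

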### Primary outcome - medication adherence

Table 2 provides an overview of study measures and outcomes. The MA calculation method has been previously described but will be briefly described here [41]. A 0.5 is assigned if the dose of the immunosuppressive medication is taken within a 3-hour window (+/-1.5 hours of the prescribed time); 0.25 is assigned if the dose of the immunosuppressive medication is not within the 3-hour window but is taken within a 12-hour window (+/-6 hours of the prescribed time), and 0 is assigned if the dose of the immunosuppressive medication is not taken within a 12-hour window (+/-6 hours of the prescribed time, i.e., if the dose was missed). On each day, an individual is assigned a score of 0, 0.25, 0.50, 0.75 or 1 points (p. 526).

**Table 2 Tab2:** Study outcomes and measures

	Screening	Intervention	Maintenance
*Inclusion Criteria*			
6-item telephone measure of cognition	√		
Primary Outcome			
Medication adherence–electronic medication monitoring	√	√	√
Secondary Outcomes			
Creatinine	√	√	√
Blood urea nitrogen	√	√	√
Acute rejection	√	√	√
Chronic rejection	√	√	√
Infection	√	√	√
Death	√	√	√
*Potential Mediators*			
Social Support		√	√
Perceived Health		√	√
Personal Systems Thinking		√	√
*Background*/*Moderating Variables*			
Medical History	√		
Demographics (ethnicity)	√		
Level of Medication Nonadherence	√		
Pillbox use	√		
*Health care costs*			
Hospitalizations, clinic, observation, and ER visits	√	√	√

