Our exploratory analyses focuses on three aims: 1) to determine whether the SystemCHANGE™ intervention is more effective than the attention-control intervention in decreasing poor health outcomes (e.g. increasing creatinine/BUN, infection, acute/chronic rejection, graft loss, death), 2) to evaluate the role of potential mediators (social support, and systems-thinking) and moderators (ethnicity perceived health and level of medication nonadherence) of MA and health outcomes in adult kidney transplant recipients receiving the SystemCHANGE™ intervention, and 3) to determine if the SystemCHANGE™ intervention is cost-effective.

We expect to observe lower levels of poor health outcomes in the SystemCHANGE™ group as compared to the control group. The dependent variables are the dichotomous outcomes such as, infection, acute and chronic rejection, graft loss, and death and numeric outcomes such as creatinine, and BUN.

The independent variable is group assignment. Chi-square tests will be applied to estimate and test the relationships between dichotomous outcome variables and the independent variable. For continuous outcomes variables t test or Mann-Whitney test will be conducted to test for group effect depending on the satisfaction of normality assumption.

Our secondary exploratory aim is to evaluate the role of potential mediators and moderators of MA and health outcomes in adult kidney transplant recipients receiving the SystemCHANGE™ intervention and recipients receiving the attention-control intervention. We hypothesize that exploring potential mediators and moderators in the analyses will enhance the interpretation of treatment effect on MA. To test for mediator effect, the dependent variable is MA and the independent variable is treatment group. Potential mediators are social support and systems thinking. Poisson regression will be applied to estimate the mediator effect [65] and the Sobel test [66] will be used to test if the mediator effect is significant. Changes in the variance with mediator in the models will be estimated and reported as part of the analysis results. To test for moderator effect, the dependent variable is MA and the independent variable is treatment group. Potential mediators are ethnicity group, perceived health and MA level (different strata). Poisson regression will be applied to estimate and test for possible moderator effect through interaction terms between the independent variable and moderator [65].

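### Poisson regression is specified for a bounded adherence rate, so model-based standard errors in the secondary, mediator and moderator analyses depend on the unit in which adherence is entered

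*Protocol article*

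**What the plan says.** The Statistical analysis section defines the outcome of the secondary analysis: "The dependent variable for these research questions are the repeated measurements of immunosuppressive MA rates at 12 time points". It then fixes the model: "Poisson regression analysis will be used for these questions. Proc Nlmixed procedure in SAS will be used for Poisson regression modeling". The tested effect is the group-by-time interaction, and on correlation it says "Repeated measures from the same Pp will be accounted for using a random effect in the model".

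The exploratory part of the same section keeps adherence as the dependent variable. For mediation, "Poisson regression will be applied to estimate the mediator effect", followed by a Sobel test. For moderation, "Poisson regression will be applied to estimate and test for possible moderator effect through interaction terms".

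The section Primary outcome - medication adherence gives the scale: "On each day, an individual is assigned a score of 0, 0.25, 0.50, 0.75 or 1 points". A monthly rate is therefore an average of quarter-point scores and cannot exceed 1.

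The article writes the rate in two units. The adherence clusters in Statistical analysis are decimals, the strata under Randomization are percentages, and the Design section attaches a percent sign to a decimal threshold.

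**The concern.** A Poisson likelihood ties the variance to the mean, and that holds only if the outcome is a count of events. An averaged score capped at 1 has no such link. Two consequences follow. The model's residual variance need not resemble the data. And because multiplying the outcome by a constant multiplies the mean by that constant but the true variance by its square, the assumed precision changes with the unit.

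The stated secondary aim is to learn when the intervention starts to work and how adherence decays. That rests on the interaction test from this model. The moderator interaction tests use the same kind of standard error, and the Sobel statistic uses the model's standard errors. Whether any of these reaches significance could turn on whether the analyst enters 0.70 or 70.

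**Working it through.** **1. The plan's own figure.** The only stated figure is 46 per group, for the primary comparison. With a 10-point difference and the stated effect size of 70 % read as 0.70 SD (implied SD 10/0.70 = 14.3 points), two-sided alpha 0.05 (sidedness is not stated) and 90 % power, the noncentral-t calculation gives 44 per arm. Dividing by the Mann-Whitney efficiency, 44/(3/π) = 46.1. The figure is reproduced and does not involve the Poisson model.

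**2. Is the Poisson variance possible on 0-1?** For mean m, Poisson imposes SD = √m. A variable confined to 0-1 cannot have an SD above √(m(1−m)). Since √m is larger for every m above 0, the assumption fails at any mean:

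| Mean | Poisson SD | Largest possible SD |
|---|---|---|
| 0.50 | 0.71 | 0.50 |
| 0.70 | 0.84 | 0.46 |
| 0.80 | 0.89 | 0.40 |
| 0.90 | 0.95 | 0.30 |

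**3. Unit dependence.** Multiplying the outcome by c leaves the log ratio unchanged and divides the Poisson standard error by √c. From proportion to percent, c = 100 and √c = 10. No assumed SD enters.

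**4. The planned interaction in closed form.** Take 46 per arm, months 1 to 12 (sum of squared deviations of month = 143), mean 0.70, and months independent given the participant with within-person SD s. The mean, s and the independence are assumptions.
- Poisson SE on 0-1, group by linear time: √(2/(46 × 0.70 × 143)) = 0.0208.
- True SE: (s/0.70) × √(2/(46 × 143)) = (s/0.70) × 0.01744. At s = 0.08 this is 0.0020.
- Ratio: √0.70/s on 0-1, and one tenth of that on 0-100.

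**5. Simulation.** 92 participants, 12 months, no group effect, 1000 runs per row, between-person SD 10 to 13 points (assumed). Ratios are model SE over true SE.

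| Within-person SD (points) | 0-1, formula | 0-1, simulated | 0-100, simulated | Type I error on 0-100, linear time | Type I error on 0-100, 11-df group-by-month |
|---|---|---|---|---|---|
| 5 | 16.7 | 17.2 | 1.72 | 0.000 | 0.00 |
| 8 | 10.5 | 10.5 | 1.05 | 0.038 | 0.02 |
| 10 | 8.4 | 8.5 | 0.85 | 0.100 | 0.23 |
| 12 | 7.0 | 7.3 | 0.73 | 0.153 | 0.52 |

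On 0-1 the type I error was 0.000 in every row. To see what that means for power: significance needs an interaction of about 1.96 × 0.0208 = 0.041 on the log scale per month. Over 11 monthly steps that is 0.45, a ratio of exp(0.45) = 1.57. If the control arm stayed at 0.70, the other arm would have to rise from 0.70 to 0.70 × 1.57 = 1.10 by month 12, above the maximum of the scale.

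**6. Does the random effect repair this?** The random-intercept Poisson likelihood was fitted to one simulated data set (within-person SD 8 points). The interaction SE was 0.02126 on 0-1 and 0.00213 on 0-100, still a factor of 10. The random-effect SD collapsed to about 0 on 0-1 and was 0.148 on 0-100. The group main effect was less sensitive: 0.073 against 0.032, a factor of 2.3.

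**7. One value per participant.** As an illustration for the mediator and moderator models, take 46 per arm, SD 14.3 points, mean 0.70 and no random effect. The true SE of the log ratio is √(2/46) × 0.143/0.70 = 0.0426. Poisson gives √(2/(46 × 0.70)) = 0.249 on 0-1 (5.9 times too large) and 0.0249 on 0-100 (0.59 of the true value, type I error about 0.25).

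**8. After correction.** With participant-clustered robust standard errors, type I error for the linear interaction was 0.042 to 0.059 across the four rows. At SD 8 points the robust SE was 0.00194 against an empirical SD of 0.00198.

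**The case against.** The best defence has four parts.

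First, the article condenses a fuller plan, which may enter adherence as a dose count with an offset, add a dispersion parameter or use an empirical variance. That stands in part: the absence of those details is not a finding. What remains is what the text does fix, a Poisson likelihood with the rate itself as dependent variable.

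Second, the size of the error depends on SDs that the article does not give. That also stands. If daily scores were independent at mean 0.70, a monthly SD could not exceed 0.458/√30, about 8.4 points, and at 8 points the percent-scale standard error is close to correct (ratio 1.05). Larger SDs need day-to-day correlation or drift, which is plausible but undocumented. Neither the tenfold unit effect nor the impossible variance on 0-1 depends on this.

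Third, a reader might infer that these tests must have either no power or an inflated error rate. The documents do not support that. If monthly adherence were entered as points from 0 to 30, the interaction standard error would be 3.14 to 1.34 times the true value for within-person SDs of 5 to 12 points. That is conservative without necessarily removing all power. The direction of the error depends on the unit and the SD.

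Fourth, a reader might infer that the trial's main result is at risk. It is not: the primary comparison uses a Mann-Whitney or t-test and the sample size rests on that. The log-ratio estimates from the Poisson model are essentially the same in any unit. That the log link permits fitted means above 100 % is a side point with no demonstrated effect on a planned test.

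**Conclusion.** The point holds for the secondary pattern analysis and for the exploratory mediator and moderator tests on adherence. The named likelihood does not fit a bounded fractional score, and its standard errors depend on a unit that the article uses inconsistently. Those two statements need no assumed SD. The size of the distortion in either unit does rest on assumptions: mean adherence near 70 %, within-person monthly SD of 5 to 12 points, and months independent given the participant. Under them the proportion scale makes the interaction test useless, and the percent scale may make it conservative, about right or anti-conservative. The participant random effect does not change this for the interaction. The point should be fixed before analysis, but it does not threaten the primary conclusion.

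**What to change.** In the secondary and exploratory parts of the Statistical analysis section, replace the Poisson likelihood for adherence with one of these:
- a fractional-logit GEE with participant-clustered sandwich standard errors; or
- a linear mixed model for monthly adherence with random intercept and slope and robust standard errors.

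At minimum, keep the log-link mean model but base all tests, including the Sobel test, on participant-clustered robust standard errors. An unstructured covariance is not needed: over 12 months it has 12 × 13/2 = 78 parameters, to be estimated from 92 participants.

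In each case fix the unit of adherence in advance, use it throughout, and report arm differences in percentage points with 95 % confidence intervals. The cost is a change of analysis wording and of the fitting procedure. No new data, visits or participants are required.
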